### **8.4.4 Clinical response analysis**

Clinical response to therapy will be assessed by the investigator at day 30. Clinical response will be based on the global assessment of the clinical presentation of the subject made by the investigator at the evaluation time point compared to the baseline assessment. Clinical outcome by the end of treatment will be cure, improvement, or failure. A clinical outcome of "cure" or "improvement" is considered a success. At the visit on day 30, the clinical outcome will be defined as successful, failure or relapse according to criteria specified in Appendix B.

"Intent to treat" and "evaluable" clinical analyses will be performed comparing clinical outcomes as defined on day 30. Ninety-five percent (95%) confidence intervals on the difference between the treatment groups in the rates of clinical success will be computed.

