## **2. Objectives**

### **2.1 Primary objective(s)**

The primary objective of this study is to determine whether a CRP guided and PCT guided treatment strategy (strategies mentioned below) can be used to safely and effectively reduce the duration of antibiotic treatment as compared to common clinical practice in patients with CAP requiring hospitalisation.

The diagnosis CAP will be made if a non-hospitalized person presents with one or more symptoms associated with a lower respiratory tract infection **and** a new infiltrate on the chest radiograph. These symptoms are: temperature greater than 38°C (100.4°F); cough with or without sputum; hemoptysis; pleuritic chest pain; dyspnea; malaise or fatigue; myalgia; gastro-intestinal symptoms; rales, rhonchi or wheezing; egophony or bronchial breath sounds.

The 3 different treatment strategies are as follows:

1. Treatment according to common practice: often a 7 day course of antibiotics.
2. Treatment with antibiotics for at least 3 days according to current guidelines, with extension of antibiotic treatment according to procalcitonin levels. Antibiotic treatment will be discontinued if the procalcitonin level is below 0.25 mcg/L **or** shows a reduction to 10% of the initial value.
3. Treatment for 3 days according to current guidelines, with extension of antibiotic treatment according to CRP levels. Antibiotic treatment will be discontinued if the value is below 100 mg/L **and** shows a reduction to 50% of the initial value.

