### **6.5 Study evaluations**

#### **6.5.1 Definitions of clinical response**

The overall clinical response will be determined by the investigator on day 30. Clinical response will be classified by the investigator as cure, failure, or indeterminate at day 30 as defined in Appendix B. When the investigator is unsure on how to score selected cases, he will consult a colleague to try and reach a consensus. Clinical evaluation of response will be based on the global assessment of the clinical presentation of the subject and compared to the baseline assessment. Clinical assessment will be based upon resolution or improvement of radiological and clinical signs of infection such as resolution of fever, disappearance or diminution in purulent sputum production, and improvement or resolution of dyspnoea, cough and leucocytosis, as well as improvement in general physical condition.

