|                                                                               | N   | Minimum | Maximum | Mean   | Std. Deviation |
| dag                                                                           | 170 | 0,00    | 42,00   | 8,7588 | 5,87499        |

We assume a mean difference of 2 days of antibiotic treatment to be clinically relevant. The results will be evaluated for a normal distribution using the kolmogorov-smirnov test. If they are normally distributed an ANOVA will be performed, with the addition of a Tukey-HSD test. If they are not normally distributed a Kruskal-Wallis test will be performed with the addition of separate Mann-Whitney U tests as post-hoc tests. The significance of these separate Mann-Whitney U tests will be corrected for multiple testing using the Bonferroni Holm method.

Using the means and standard deviations mentioned above, with an alpha of 0.025 (corrected for multiple testing using the Bonferroni Holm method) and a  $\beta$  of 0.20 this would require a total of 139 patients per group if the results are normally distributed and 146 patients per group if they aren't. A total of 156 patients per group will be included, to account for loss to follow-up, deaths etc. Which amounts to a total of 468 patients. Calculation was done by using the program G-power.

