## **8.4 Methods of analysis**

### **8.4.1 General statistical considerations**

All data will be collected and analysed using SPSS statistics 20.

Statistical analysis will be performed on an intent-to-treat basis by an independent statistician. All continuous variables will be tested for normal distribution with the Kolmogorov-Smirnov test for normal distribution. The Student-t test will be used for normally distributed variables, the Mann-Whitney U test for not normally distributed variables and the  $\chi^2$  test for dichotomous variables. The software package SPSS 20 for Windows (IBM-SPSS Inc., Chicago, Illinois, USA) is available for statistical analysis. A value of  $p < 0.05$  will be considered significant.

All data will be collected and analysed using SPSS statistics 20.

Clinical response will be analysed by using the Kruskal wallis test.

Duration of treatment and in-hospital stay will be expressed as means with a 95% confidence interval. Sub-group analyses will be performed on patients with severe CAP according to the CURB criteria and patients with non-severe CAP.

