### **8.4.3 Efficacy analyses**

The primary efficacy analysis will be duration of antibiotic treatment.

The secondary efficacy analyses will be clinical response on day 30, length of hospital stay, time to clinical stability, relapse rate and overall mortality on day 30 and day 90.

Possible confounders (e.g. co-morbidities, type of pathogen etc.) will be assessed. Where appropriate a correction will be performed.

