## ***Appendix B: Definition of clinical and radiological responses***

### **Clinical response**

#### *Test of cure*

Cure —resolution or improvement of symptoms and clinical signs related to pneumonia without the need for additional or alternative antibiotic therapy

Failure —persistence or progression of all signs and symptoms of the acute process after randomisation or the development of a new pulmonary or extrapulmonary respiratory tract infection, or the progression of abnormalities on chest radiograph after randomisation, or death due to pneumonia, or the inability to complete the study owing to adverse events

Indeterminate —patient receives less than 80% of the study drug for reasons other than clinical failure, a concomitant infection outside the respiratory tract requiring antibiotic treatment, lost to follow-up, or death unrelated to the primary diagnosis

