#### *Late follow-up*

Cure —continued resolution or improvement of symptoms and clinical signs related to pneumonia without the need for additional or alternative antibiotic therapy

Recurrence —new or worsened signs and symptoms of pneumonia or another respiratory tract infection in a patient who was cured at the visit for test of cure

Indeterminate —lost to follow-up, a concomitant infection outside the respiratory tract requiring antibiotic treatment, or death unrelated to the primary diagnosis

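### Day-30 clinical response has two incompatible category sets, is assigned a rank test that needs an order it lacks, and gives no criterion for 'safely' in the primary objective

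*Protocol*

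**What the plan says.** **Objective.** Section 2.1 asks whether the marker-guided strategies "can be used to safely and effectively reduce the duration of antibiotic treatment as compared to common clinical practice". Section 6.1.1 repeats safety as part of the main study parameter.

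**What is powered.** Section 8.4.3: "The primary efficacy analysis will be duration of antibiotic treatment". The sample size in sections 4.4 and 8.1 concerns duration only.

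**Day-30 response.** Section 6.5.1: "Clinical response will be classified by the investigator as cure, failure, or indeterminate at day 30 as defined in Appendix B". Section 8.4.4: "At the visit on day 30, the clinical outcome will be defined as successful, failure or relapse according to criteria specified in Appendix B". Section 8.4.4 also gives a separate end-of-treatment scale of cure, improvement or failure, and counts the first two as success.

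**Appendix B.** It holds two scales, neither tied to day 30. Test of cure has cure, failure and indeterminate. The first limb of failure is "persistence or progression of all signs and symptoms of the acute process after randomisation". Late follow-up has cure, recurrence and indeterminate, with recurrence arising only "in a patient who was cured at the visit for test of cure".

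**Analysis.** Section 8.4.1: "Clinical response will be analysed by using the Kruskal wallis test". Section 8.4.4 adds 95% confidence intervals for between-group differences in clinical success, in the intention-to-treat and evaluable sets. Sections 8.4.1 and 8.5 assign chi-square to dichotomous variables and set significance at p < 0.05.

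**The concern.** The protocol's own risk form (Appendix A) names the return of symptoms after stopping as the risk of shortened treatment, so day-30 response carries much of the weight of *safely*. Three things weaken it.

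1. Sections 6.5.1 and 8.4.4 cannot both be followed, and the appendix they share does not settle which applies.
2. The test assigned to the outcome ranks its categories, but the 6.5.1 categories have no natural ranking.
3. Nothing states what result would count as safe. The plan's only general threshold is p < 0.05, and in a trial of this size a non-significant difference in success is compatible with a real loss.

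At stake is whether the safety half of the primary objective can be concluded from a pre-specified analysis. The duration analysis is unaffected.

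**Working it through.** **Plan's own figure.** Inputs from section 8.1: a 2-day difference; SD 4.80257 (PCT) and 5.87499 (control); power 0.80; "with an alpha of 0.025 (corrected for multiple testing using the Bonferroni Holm method"), taken as two-sided.
- SD = √[(4.80257² + 5.87499²)/2] = 5.366.
- Normal approximation: n = 2 × (2.241 + 0.842)² × 5.366² / 2² ≈ 137. The exact t-test gives 139, as stated.
- Mann-Whitney with efficiency 3/π: 139 × π/3 = 145.6, so 146, as stated.

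The stated sizes are therefore right, but only for duration. No success rate, margin or power is given for clinical response.

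**Categories side by side.**

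| Source | Time point | Categories |
|---|---|---|
| 6.5.1 | day 30 | cure / failure / indeterminate |
| 8.4.4 | day 30 | successful / failure / relapse |
| 8.4.4 | end of treatment | cure / improvement / failure |
| Appendix B, test of cure | not stated | cure / failure / indeterminate |
| Appendix B, late follow-up | not stated | cure / recurrence / indeterminate |

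**A worked patient.** The patient improves, stops antibiotics, worsens, restarts, and is better by day 30.
- *Test of cure:* not a cure, because further antibiotics were needed. A failure only if all signs persist or progress, or another limb applies (new respiratory infection, radiographic progression, death due to pneumonia, inability to complete because of adverse events). Indeterminate only if one of its own conditions is met.
- *Late follow-up:* a recurrence only after cure at an earlier test-of-cure visit. Neither the body text nor Appendix C schedules one; the index lists a Day 14 section whose text is absent.
- *Section 8.4.4:* a relapse, but the appendix it cites has no such criterion.

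**Coding dependence of Kruskal-Wallis.** Made-up counts of cure/failure/indeterminate in three arms of 156: 130/6/20, 120/26/10, 128/10/18.

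| Order imposed | H | p |
|---|---|---|
| cure, failure, indeterminate | 1.13 | 0.57 |
| cure, indeterminate, failure | 3.82 | 0.15 |
| failure, cure, indeterminate | 16.69 | 0.0002 |

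The data are the same in each row; only the coding differs.

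**Precision and power for success.** n = 156 per arm (section 8.1; 3 × 156 = 468. Section 4.4 gives 148, but 3 × 148 = 444). Success rates p are assumed.
- SE = √[2p(1−p)/156]; half-width = 1.96 × SE.
- Power to detect a 5-point loss, two-sided 0.05: Φ[(0.05 − 1.96 × SE₀)/SE₁], where SE₀ uses the average of p and p − 0.05, and SE₁ uses the two separate rates. At p = 0.90: (0.05 − 1.96 × 0.03745)/0.03734 = −0.627, so 0.265.
- Power for a 10-point margin with equal true rates, one-sided 0.025: Φ(0.10/SE − 1.96). At p = 0.90: 0.10/0.03397 − 1.96 = 0.984, so 0.84.
- Smallest margin with 80% power: (1.96 + 0.842) × SE.

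| Assumed success | SE | Half-width (points) | Power, 5-point loss | Power, 10-point margin | Margin with 80% power (points) |
|---|---|---|---|---|---|
| 80% | 0.0453 | 8.9 | 18% | 60% | 12.7 |
| 85% | 0.0404 | 7.9 | 21% | 70% | 11.3 |
| 90% | 0.0340 | 6.7 | 27% | 84% | 9.5 |

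A simulated three-arm Kruskal-Wallis test on success versus non-success, with one arm 5 points lower, gives the same 18/21/27%.

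**The case against.** Much can be said for the plan.

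- **Relapse is not ignored.** A reader might infer that a relapse with restarted antibiotics fits no category anywhere, or drops out of the success count. The protocol does not support that. Section 8.4.4 names relapse as a day-30 outcome, section 2.2 defines it, and relapse rate is its own secondary analysis in 8.4.3. Such a patient is a non-success on either day-30 scale: a relapse is not successful, and someone needing more antibiotics is not a cure. What stands is narrower: the patient may have no label under 6.5.1 and Appendix B, and 8.4.4 points to a criterion the appendix lacks.
- **A difference test is not the only analysis.** The confidence intervals in 8.4.4 are the right tool, and no passage says that non-significance means safe. What stands is that nothing says how to read the interval.
- **The end-of-treatment scale is not a third day-30 definition.** It carries its own time point, and its improvement category is absorbed by the Appendix B wording of cure. It is also ordered, so Kruskal-Wallis would be defensible there. The objection to that test applies to cure/failure/indeterminate.
- **The 80% criterion** in indeterminate need not catch early stoppers. A stop directed by the marker rule can be read as completing the planned course. The wording leaves this open and no more.
- **Deaths judged unrelated** are still counted in the overall mortality analyses of 8.4.3.
- **The Day 14 section** in the index may be lost text, so the missing test-of-cure visit is not certain. Appendix C, however, has no day-14 column.

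**Conclusion.** The point holds in this form. Two day-30 category sets cite one appendix that defines neither *successful* nor *relapse*; the assigned rank test depends on arbitrary coding of an unordered scale; and *safely* has no criterion.

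On size, at 156 per arm a non-significant comparison would accompany a true 5-point loss in roughly three-quarters to four-fifths of trials (power 18/21/27% at assumed success of 80/85/90%). All precision figures rest on assumed success rates, because the protocol gives none.

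A reader might also infer that the existing sample supports a 10-point margin without extra patients. That holds only near 90% success (84% power). At 85% and 80% the power is 70% and 60%, and 80% power would need 201 and 252 per arm. These figures make no allowance for two comparisons with control.

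**What to change.** 1. **One classification.** Reconcile 6.5.1, 8.4.4 and Appendix B into a single day-30 scale. State for the intention-to-treat analysis whether relapse, restart of antibiotics and each kind of indeterminate case count as success or non-success. Clarify that a stop directed by the marker rule is not receipt of under 80% of study drug.
2. **One analysis.** Delete Kruskal-Wallis for clinical response. Use binary success, with chi-square and the 95% confidence interval already planned, for each marker arm against control.
3. **A basis for *safely*.** Read that interval against a margin that the sponsor justifies before data are seen. Otherwise, limit the claim to the largest deficit the interval excludes.
4. **State the precision.** Give the expected half-width (about 8.9/7.9/6.7 points at 80/85/90% success) and the power for any margin chosen (60/70/84% for 10 points), with the success rate assumed.

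The cost is wording, plus an agreed margin if one is used; item 3 can be met without more patients by limiting the claim. The downside is a narrower statement about safety.

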### **8.5 Methodology**

Statistical analysis will be performed on an intent-to-treat basis by the investigator and will be checked by an independent statistician. All continuous variables will be tested for normal distribution with the Kolmogorov-Smirnov test for normal distribution. The Student-t test will be used for normally distributed variables, the Mann-Whitney U test for not normally distributed variables and the  $\chi^2$  test for dichotomous variables. The software package SPSS 20 for Windows (IBM-SPSS Inc., Chicago, Illinois, USA) is available for statistical analysis. A value of  $p < 0.05$  will be considered significant.

## **9. Ethical considerations**

### **9.1 Regulation statement**

This study will be conducted in compliance with Good Clinical Practice (GCP), including the International Conference on Harmonization (ICH) guidelines and the most recent version of the Declaration of Helsinki.

All amendments to the protocol and informed consent forms must be reviewed by the local Independent Ethics Committee for approval before being implemented. In the event of any deviation from the protocol, the investigator must document the nature of and rationale for the deviation. Informed consent must take place prior to any study specific procedure or test. Written signed and dated informed consent will be obtained from each subject (or his/her legally acceptable representative) in accordance with GCP and with local regulatory and legal requirements. The completed informed consent will be retained by the investigator as part of the study records.

### **9.2 Recruitment and consent**

Patients or their legal representatives will be asked to participate in this study by the attending physician or the investigator at the time of hospital admission. All patients will receive the patient information letter and informed consent form. They will be given one hour to consider their decision. Prior to consent blood tests may be performed and antibiotics can be started, since this is all part of regular care and in the patients interest.

### **9.3 Benefits and risks assessment, group relatedness**

Low risk study according to the risk-classification as designed by the Dutch Foundation of University Medical Centres. The full risk classification (in Dutch) can be found in Appendix A.

### **9.4 Compensation for injury**

The sponsor/investigator has a liability insurance which is in accordance with article 7, subsection 6 of the WMO.

The sponsor (also) has an insurance which is in accordance with the legal requirements in the Netherlands (Article 7 WMO and the Measure regarding Compulsory Insurance for Clinical Research in Humans of 23th June 2003). This insurance provides cover for damage to research subjects through injury or death caused by the study.

1. € 450.000,-- (i.e. four hundred and fifty thousand Euro) for death or injury for each subject who participates in the Research;
2. € 3.500.000,-- (i.e. three million five hundred thousand Euro) for death or injury for all subjects who participate in the Research;
3. € 5.000.000,-- (i.e. five million Euro) for the total damage incurred by the organisation for all damage disclosed by scientific research for the Sponsor as 'verrichter' in the meaning of said Act in each year of insurance coverage.

The insurance applies to the damage that becomes apparent during the study or within 4 years after the end of the study.

## ***10. Administrative aspects, monitoring and publication***

### ***10.1 Handling and storage of data and documents***

All data will be collected by the researcher on the Case Report Form (CRF). The data will be entered into a database, where subjects will be assigned a study number. Their personal information will not be entered into the database. A separate subject identification list will be kept by the sponsor in case the study data needs to be linked to individual subjects.

All study data will be kept for 15 years. Blood samples and sputum samples will be stored for 3 years, to conduct future research regarding inflammatory biomarkers and genetic polymorphisms of corticosteroid receptors.

### ***10.2 Monitoring and quality assurance***

The conduct of the study and data entries will be monitored by an internal monitor. This will be done by [name] who will select a sample of cases and check them for irregularities. If any are found, the monitor may choose to select a larger sample or review all available data. He will report the irregularities to the sponsor who is responsible for correcting any mistakes.

All adverse events will be analysed periodically by the statistician of the DSMB. If adverse events of a particularly serious type are more common in the experimental arm compared to the control arm he will inform the sponsor and other members of the DSMB which may then take actions as described in chapter 7.5.

All serious adverse events will be reported to the accredited METC.

### ***10.3 Amendments***

Amendments are changes made to the research after a favourable opinion by the accredited METC has been given. Non-substantial amendments will not be notified to the accredited METC and the competent authority, but will be recorded and filed by the sponsor. All other amendments will be notified to the METC that gave a favourable opinion.

### ***10.4 Annual progress report***

The sponsor/investigator will submit a summary of the progress of the trial to the accredited METC once a year. Information will be provided on the date of inclusion of the first subject, numbers of subjects included and numbers of subjects that have completed the trial, serious adverse events, other problems, and amendments.

### ***10.5 End of study report***

The investigator will notify the accredited METC of the end of the study within a period of 8 weeks. The end of the study is defined as the last patient's last visit. In case the study is ended prematurely, the investigator will notify the accredited METC within 15 days, including the reasons for the premature termination. Within one year after the end of the study, the investigator/sponsor will submit a final study report with the results of the study, including any publications/abstracts of the study, to the accredited METC.

## ***Appendix A: Risico-classificatie ten behoeve van monitoring van investigator initiated onderzoek***

| Toegevoegd risico                                                                           |                                                                                                                                                                                                                                                                                            |
|----------------------------------------------------------------------------------------------------|--------------------------------------------------------------------------------------------------------------------------------------------------------------------------------------------------------------------------------------------------------------------------------------------|
| Wat is het toegevoegde risico van de onderzoekshandelingen voor de veiligheid van de proefpersoon? | Er zal enkele malen vaker bloed afgenomen worden in vergelijking met de reguliere klinische zorg.
Daarnaast zal de duur van de antibiotische therapie in 2 groepen verkort worden als de bloedwaarden dit toelaten.
Mochten patiënten toch weer zieker worden zal dit hervat worden. |

| Frequentie/schade        |                                                                                                                                                                                                                                                                                                                                                                                                                                                                                                                                                                                                                                                                                                                                                                          |
|---------------------------------|--------------------------------------------------------------------------------------------------------------------------------------------------------------------------------------------------------------------------------------------------------------------------------------------------------------------------------------------------------------------------------------------------------------------------------------------------------------------------------------------------------------------------------------------------------------------------------------------------------------------------------------------------------------------------------------------------------------------------------------------------------------------------|
| Hoe groot is de kans op schade? | klein                                                                                                                                                                                                                                                                                                                                                                                                                                                                                                                                                                                                                                                                                                                                                                    |
|                                 | 
Toelichting:
De complicaties van een vena punctie betreffen voornamelijk pijn, eventueel nabloeden en hematoom vorming. Dit is vrijwel altijd self-limiting en behoeft over het algemeen geen aanvullende therapie.
 
Het risico van een verkorte behandeling met antibiotica is dat patiënten na het staken van de therapie mogelijk weer klachten krijgen. De therapie zal niet gestaakt worden als de behandelend arts dit onveilig acht.
Over het algemeen geldt dat het staken in een gecontroleerde omgeving gebeurt en de behandeling direct weer hervat kan worden als de behandelend arts dit besluit. Met patiënten in de thuissituatie zal worden afgesproken dat ze altijd direct contact op kunnen nemen met de dienstdoende assistent.
 |

| Risico onderzoekshandeling                                                                                     |                                                                                                                                                                                                                                                                                                                                                  |
|-----------------------------------------------------------------------------------------------------------------------|--------------------------------------------------------------------------------------------------------------------------------------------------------------------------------------------------------------------------------------------------------------------------------------------------------------------------------------------------|
| Hoeveelheid kennis en ervaring met de interventie, het geneesmiddel, voedingsmiddel of medisch hulpmiddel bij mensen? | Een venapunctie is een routine medische handeling waar veel ervaring mee is.
Er zijn reeds studies gedaan met het staken van antibiotica op geleide van het procalcitonine, dit bleek veilig en effectief.
Retrospectief onderzoek laat criteria voor de CRP groep zien die theoretisch net zo veilig en effectief zijn.                   |
| Bekende risico's:                                                                                                     | Hematoom, nabloeding, pijn.
Bij de antibiotica groepen: theoretisch meer ziekte verschijnselen na vroeger staken.                                                                                                                                                                                                                             |
| Kans op het optreden van onbekende risico's:                                                                          | Zeer klein.                                                                                                                                                                                                                                                                                                                                      |
| Ernst van de mogelijke nadelige effecten/mate van schade:                                                             |  lichte schade

Toelichting:
Hematoom, nabloeding en pijn zijn over het algemeen self-limiting zonder aanvullende therapie of diagnostiek.
Indien patiënten zieker worden na staken van antibiotica, zullen zij hun kuur mogelijk weer moeten hervatten zoals in de reguliere praktijk ook gebeurt.
 |
| Voorspelbaarheid van nadelig effect:                                                                                  | Direct merkbaar.                                                                                                                                                                                                                                                                                                                                 |
| Mogelijkheid om ongewenste effecten te beheersen:                                                                     | Bij nabloeding is afdrukken over het algemeen voldoende.
Bij zieker worden zal de antibiotica herstart worden.                                                                                                                                                                                                                                |

|                                                     |                                                                                                                      |
|-----------------------------------------------------|----------------------------------------------------------------------------------------------------------------------|
| Reversibiliteit van de mogelijke nadelige effecten: | Bij de vena punctie: volledig reversibel.
Bij antibiotica: volledig reversibel na eventueel aanvullende therapie. |
| Lichamelijke belasting (pijn, ongemak):             | Pijn.
Mogelijk meer ziekteverschijnselen.                                                                         |
| Psychische belasting (angst, stress):               | Mogelijk stress voor venapunctie.                                                                                    |

| Kenmerken onderzoekspopulatie                               |                                                                                                                                          |
|--------------------------------------------------------------------|------------------------------------------------------------------------------------------------------------------------------------------|
| Kwetsbaarheid (ernstig zieken, kwetsbare ouderen, jonge kinderen): | Ernstig zieke patiënten die een ICU opname behoeven zijn uitgesloten van deelname.
Ouderen zullen wel deel mogen nemen aan de studie. |

| Maatschappelijke risico's                                                |                                                                                                                  |
|---------------------------------------------------------------------------------|------------------------------------------------------------------------------------------------------------------|
| Voor de proefpersoon (privacy, stigmatisering, uitsluiting van verzekering):    | Geen.                                                                                                            |
| Voor het onderzoek (maatschappelijk draagvlak, gevoeligheid van het onderzoek): | Mogelijk eerste stap in nieuwe behandelstrategie op populatieniveau. Geen controverse op maatschappelijk niveau. |

| Risico's samenhangend met onderzoeksopzet en –uitvoering (risico op protocol violations) |           |
|-------------------------------------------------------------------------------------------------|-----------|
| Complexiteit van het protocol:                                                                  | Eenduidig |
| Aantal te includeren proefpersonen:                                                             | 468       |

| Conclusie risico-classificatie                 |                                                                                                                                                                                                                                                                                                                                                                                                                                                           |
|-------------------------------------------------------|-----------------------------------------------------------------------------------------------------------------------------------------------------------------------------------------------------------------------------------------------------------------------------------------------------------------------------------------------------------------------------------------------------------------------------------------------------------|
| Maak aan de hand van tabel 1 een keuze uit de opties: |  verwaarloosbaar risico                                                                                                                                                                                                                                                                                                                                                                                                           |
| Geef een toelichting op de gemaakte keuze.            | Toelichting:
Kleine kans op schade, die licht tot matig kan zijn echter wel reversibel is. Patiënten zullen bij toename van ziekteverschijnselen na eerder staken van antibiotica behandeld worden volgens het normale klinische pad. Dit houdt in dat zij vervolgens hetzelfde behandeld worden als patiënten die ervoor kiezen geen deel te nemen aan het onderzoek. Wij verwachten niet dat dit de opnameduur of (reguliere) behandelduur verlengt. |

Tabel 1. Risicoclassificatie (verwaarloosbaar risico, matig risico, hoog risico) in relatie tot de kans op schade en de ernst van die schade.

| Grootte van kans /
Mate van schade | Lichte schade             | Matige schade             | Ernstige schade |
|---------------------------------------|---------------------------|---------------------------|-----------------|
| Kleine kans                           | Verwaarloosbaar
risico | Verwaarloosbaar
risico | Matig risico    |
| Matige kans                           | Verwaarloosbaar
risico | Matig risico              | Hoog risico     |
| Grote kans                            | Matig risico              | Hoog risico               | Hoog risico     |

